## Abstract

**Clinical trial registration:**

https://clinicaltrials.gov/study/NCT07305298, identifier NCT07305298.

## Introduction

1

Sensory impairments, including vision loss, are a part of normal aging that is associated with additional aging-related diseases including those characterized by reduced contractile activity, as in overactive bladder (OAB) wherein urgency and frequent micturition are driven by a multitude of anatomical, metabolic and psychological causes. Among vision impairments proliferative retinopathies including neovascular age-related macular degeneration (wet AMD) pose a significant global burden on individuals, families, and healthcare systems (1). Wet AMD is a major cause of vision loss in elderly people, with an increase in its prevalence in the population over 75 years old. Its estimated increase of about 47% from 2020 to 2040 (2) represents a significant burden to healthcare systems, both in terms of medical treatment and non-medical related costs, such as social services (3). Intravitreal injection of anti-vascular endothelial growth factor (anti-VEGF) is approved for wet AMD. Anti-VEGFs are effective in reducing exudation, but they require frequent injections that, on the other hand, might not be decisive in providing a solution.

Wet AMD is preceded by dry AMD, which is characterized by a gradual degeneration of macular cells and the presence of lipid deposits beneath the retina both contributing to central vision loss. According to the global percentage of dry AMD progression to wet AMD, around 10–15% of patients with dry AMD progress to the wet form (4). Although there is no cure for dry AMD, the pipeline of new treatments to slow its progression is expanding. Once wet AMD is established, anti-VEGF therapy is intended to manage rather than cure wet AMD with most patients experiencing sight loss over time despite regular treatment. Preventing conversion, therefore, has better prognostic value for sight. A number of modifiable risk factors have been found to be effective in slowing AMD progression, such as smoking cessation, and dietary and nutraceutical supplements. In this respect, nutraceutical treatments might limit eye disease progression (5, 6). Among them resveratrol has emerged as a promising agent for mitigating retinal damage (7, 8). Some therapeutic agents have also been licensed for eyes with dry AMD including complement factor inhibitors, which, on the other hand, are only available for individuals with late-stage dry AMD (9). There exists a need for drugs for earlier stages of dry AMD that effectively reduce the risk of progression. Targeting oxidative stress and chronic inflammation might represent an effective treatment as their complex interplay plays a key role in retinal diseases (10).

Potential concomitance between AMD and OAB gave rise to the possibility of investigating whether a therapy that efficiently counteracts OAB may also act on dry AMD progression to wet AMD. As for wet AMD, the global prevalence of OAB is expected to increase by 10.6% from 2020 to 2030 with an increasing trend depending on obesity, gender and age (8). While anticholinergics have been the cornerstone of OAB treatment for decades, their use has consistently been challenged by issues related to side effects and lack of bladder selectivity (11). In particular, there is indication that eye diseases including glaucoma (12) and dry eye disease (13) might occur as side effects of anticholinergic drug administration in OAB patients.

Mirabegron targeting the beta 3 adrenoceptor (β3-AR) is a commonly used drug for OAB, with similar efficacy but fewer side effects than anticholinergic drug options (14). Compared to anticholinergic drugs, mirabegron improves storage function without affecting voiding, thus increasing its therapeutic effectiveness.

In proliferative retinopathies, preclinical data suggest that β3-ARs are involved in retinal vasodilation and are upregulated in ischemic conditions (15). Therefore, potentiating the effect of β3-AR through drug options may be protective against retinal proliferative disorders (such as wet AMD or diabetic retinopathy). Although no human evidence currently exists to support the biological effect of mirabegron on dry AMD progression, in recent studies in OAB patients with healthy eyes, treatment with mirabegron has been demonstrated to be well tolerated at the eye level (16). In addition, mirabegron has been found to increase choroidal thickness as an index of its potential efficacy on choroidal vascularity (17). Overall, these findings encouraged us to follow the path of repurposing mirabegron in patients with AMD treated for OAB to possibly prevent dry AMD progression to wet AMD.

In the present study we hypothesized that the use of mirabegron for concomitant diseases is associated with a reduced risk of progression of AMD. To this aim, we will investigate the effects of mirabegron in patients concomitantly affected by OAB and dry AMD to evaluate its impact on slowing down AMD progression. The potential efficacy of mirabegron on AMD progression will be compared with that of solifenacin, an anticholinergic medication conventionally used to treat OAB. In this respect, the effects of anti-cholinergic drugs in healthy eyes of OAB patients are controversial with a reduction of intraocular pressure by solifenacin as reported by Olcucu et al. (18) although no effects were previously determined by Sekeroglu et al. (19).

## Materials and methods

2

### Study design and participants: inclusion, exclusion and drop out criteria

2.1

We planned an observational double arm non-randomized study in two centers to compare the safety and efficacy of either mirabegron (50 mg/day) or solifenacin (5 mg/day) in OAB patients. The protocol provides that ophthalmologists will be blinded regarding which patients have been treated with both drugs. We planned to enroll 312 subjects aged between 50 and 80 years with a diagnosis of early or moderate dry AMD, according to ARDS classification, and OAB. The patients will be enrolled at the Department of Ophthalmology of the University of Lublin, Poland and the University of Naples Federico II, Italy from December 2025 to October 2026. All patients will be followed for a 12-month period. The study will be conducted in compliance with the tenets of the Declaration of Helsinki, accepted by the local Ethics Committee, protocol numbers 2025a45673 at the University of Naples Federico II, Italy and KE-0379/97/2025 at the University of Lublin, Poland.

All study participants will provide written informed consent prior to enrollment and for the use of their clinical data for scientific research in an anonymized manner. Inclusion and exclusion criteria are summarized in Table 1.

**Table 1 tab1:** Inclusion and exclusion criteria.

Inclusion criteria
Age 50–80-year-old
Patients with early or moderate dry AMD in one or both eyes
Patients with wet AMD in the other eye
OAB treated for at least 6 months with either mirabegron or solifenacin
BCVA > 65 EDTRS letters
Exclusion criteria
Any contraindication to β-agonists or anticholinergics
Allergy to β-agonists or anticholinergics
Uncontrolled hypertension; tachycardia; atrial fibrillation; long QT or concomitant treatment with drugs that cause lengthening of the QT interval
Patients exposed to experimental drugs other than mirabegron or solifenacin, complement factor inhibitors, photobiomodulation therapy, transscleral lutein iontophoresis therapy or recent surgery (e.g., 3 months)
Recurrent urinary infections
Renal or hepatic failure
Signs of ocular inflammation
Any other ophthalmic diseases such as dry eye, glaucoma, acute or chronic uveitis, advanced cataract
Pregnancy

AMD, age-related macular degeneration; OAB, overactive bladder; BCVA, best corrected visual acuity; EDTRS, early treatment diabetic retinopathy study; QT interval, the time from the start of the Q wave to the end of the T wave in an electrocardiogram.

The unit of analysis will be the eye. When both eyes meet eligibility criteria, both eyes will be included. The study will stop if severe hypertension, tachycardia, or atrial fibrillation develops; in this case, the opportunity to reduce the dose of mirabegron may be considered. The patient will have the right to withdraw their consent at any point during the study. Mirabegron displays no significant increase in major adverse cardiovascular events with a cardiovascular profile almost comparable to that of antimuscarinic agents. In our study, the safe profile of a 50 mg dosage will be associated with an increase of approximately 1 bpm for heart rate and 0.4–0.6 mmHg for systolic/diastolic blood pressure.

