### Study procedures and outcomes: duration of the treatment and follow up

2.2

In order to compare the proportions of solifenacin and mirabegron groups, the estimated sample size for each group has been calculated as 156 participants considering a normal distribution, an *α* error of 0.05 and a power of 80 percent. To evaluate mirabegron safety, cardiac and respiratory parameters (heart rate, blood pressure, oxygen saturation, respiratory support) will be monitored during every study visit. After obtaining informed consent and after the screening visit, at Baseline (T0) all patients will be evaluated with a complete ophthalmic examination. BCVA will be assessed based on the refractive values obtained using an autorefractometer (Huvitz autoref/keratometer HRK-1 Huvitz Co. Ltd., Republic of Korea), in agreement with Early Treatment Diabetic Retinopathy Study (ETDRS) charts. Intraocular pressure measurements will be acquired using the same device. Additionally, slit lamp examination and fundus examination by indirect ophthalmoscopy will be performed in all patients. As part of the imaging protocol, all patients will be evaluated using spectral domain optical coherence tomography (SD-OCT) and fundus autofluorescence (FAF) (SD-OCT Spectralis, Heidelberg Engineering, Heidelberg, Germany). Microperimetry will be performed using MP-1 microperimetry (Nidek Instruments Inc., Padova, Italy). All patients will be evaluated at T0, 6- and 12-months follow-up, with a complete ophthalmic examination, including SD-OCT, FAF, and microperimetry, and monitoring for any signs of ocular inflammation and/or any adverse events.

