Assuming a 12% progression rate in the solifenacin group and a 3% progression rate in the mirabegron group at 12 months (absolute difference 9%), with *α* = 0.05 (two-sided) and power = 80%, the required sample size is n ≈ 134 participants per group (net, without accounting for dropouts), computed using the standard formula for comparison of two proportions. The choice of the absolute difference of 9% is not based on clinical data as no clinical trials using either solifenacin or mirabegron to verify the rate of dry AMD progression to the wet form have been performed. This absolute difference was selected as a clinically meaningful planning effect size (Number Needed to Treat ≈ 11 over 12 months). Because eligibility and outcomes are defined at the eye level and participants may contribute with one or two eligible eyes, this calculation should be considered a planning approximation; all inferential analyses will account for within-participant correlation using robust standard errors clustered by participants.

To allow for an expected 15% dropout/non-compliance rate, the enrollment target was increased accordingly, yielding n ≈ 157 participants per group (314 total). For reporting and logistical reasons this has been pragmatically rounded to 156 participants per group (312 total); the protocol will state that this figure includes an allowance for approximately 15% attrition.

The sample size was computed according to the classical formula for two independent proportions:

$$n=\frac{\left(Z_{1-\frac{\alpha }{2}}\sqrt{2p(1-p)}+Z_{1-\beta }\sqrt{p_{1}(1-p_{1})+p_{2}{\left(1-p_{2}\right)}^{2}}\right)}{{\left(p_{1}-p_{2}\right)}^{2}}$$

Where *p*_1_ = 0.12, *p*_2_ = 0.03, *p* = (*p*_1_ + *p*_2_)/2, *α* = 0.05, and 1-*β* = 0.80. The resulting net sample size is approximately n ≈ 134 per group; after adjusting for ~15% attrition the enrollment target is *n* ≈ 157per group (rounded for the protocol to 156 per group).

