All statistical analyses will be done using Python in the Google Colab cloud computing environment and/or SPSS (version 31). The primary confirmatory timepoint will be 12 months. To control type 1 error across the pre-specified primary endpoints, *p*-values will be adjusted using the Holm procedure (two-sided). Statistical significance will be set at a two-sided α = 0.05. Analyses will be conducted using exposure-defined (as-treated) and protocol-adherent approaches, rather than randomized intention-to-treat terminology. Continuous variables will be summarized as mean ± standard deviation or median with interquartile range, depending on the data distribution assessed by the Shapiro–Wilk test. Categorical variables will be presented as frequencies and percentages. Baseline characteristics will be described and group balance will be assessed using standardized differences, rather than relying on significance testing of baseline differences.

The primary outcome measures include conversion to wet AMD at 12 months, and outer retinal morphology parameters obtained from SD-OCT and FAF, including RPD type, ONL thickness, ChT, CMT, and FAF changes. These will be analyzed using mixed-effects models to account for repeated measures at T0, 6 months, and 12 months, with fixed effects including treatment group, time, and treatment×time interaction. Robust standard errors clustered by participants will be used to account for correlation between eyes from the same participant. Adjustments will be made for baseline BCVA, age, sex, AMD stage, contralateral wet AMD status (yes/no), and other relevant factors. If assumptions of normality are not met, appropriate non-parametric methods or robust modeling approaches will be used.

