Secondary outcomes will consist of changes in BCVA (ETDRS letters) and mean MS (microperimetry). These will be analyzed using the same modeling method, with post-hoc pairwise comparisons adjusted for multiple testing using the Bonferroni method. Given the non-randomized design, primary analyses will use a pre-specified adjusted model including key baseline prognostic factors (age, sex, baseline BCVA, AMD stage/severity, comorbidities, baseline symptom severity, and contralateral wet AMD status), and results will be reported as effect estimates with 95% confidence intervals. Safety parameters (heart rate, blood pressure, oxygen saturation, need for respiratory support) will be reported as the number and percentage of patients with pathological values, without correlation to other variables. Adverse event rates will be compared using χ^2^ or Fisher’s exact tests.

Extreme values will be checked for plausibility and kept unless classified as data entry mistakes or physiologically unlikely. Missing data will be managed according to their missingness pattern, and sensitivity analyses will be conducted to assess the reliability of the results. Exploratory subgroup analyses will be performed according to AMD stage (early vs. moderate). Sensitivity analyses will exclude participants who stop taking mirabegron before 6 months or require a dose adjustment. In Figure 1, trial flow is schematically represented.

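### The cardiovascular stopping rule attaches two incompatible actions to one event and should keep the participant in eye follow-up; as a lesser point, one sensitivity analysis excludes early stoppers of mirabegron only

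*Protocol article*

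**What the plan says.** The stopping rule is in section 2.1, whose heading announces inclusion, exclusion and drop-out criteria. It reads "The study will stop if severe hypertension, tachycardia, or atrial fibrillation develops; in this case, the opportunity to reduce the dose of mirabegron", and the sentence ends by leaving that reduction optional. No level (participant, group or trial) is given. No dose change is mentioned for solifenacin.

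Four other statements bear on it:

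- Section 2.3, on the time of the primary analysis: "The primary confirmatory timepoint will be 12 months".
- Section 2.2, on visits: "All patients will be evaluated at T0, 6- and 12-months follow-up, with a complete ophthalmic examination".
- Section 2.3, on attrition: "To allow for an expected 15% dropout/non-compliance rate, the enrollment target was increased accordingly".
- Table 1, on prior exposure: "OAB treated for at least 6 months with either mirabegron or solifenacin".

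The sensitivity analysis is described near the end of section 2.3: "Sensitivity analyses will exclude participants who stop taking mirabegron before 6 months or require a dose adjustment". The same section also plans as-treated and protocol-adherent analyses and does not restrict either to one group.

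**The concern.** The stopping rule cannot be carried out as written, because one event leads to two actions that exclude each other. Two centres are enrolling. One could withdraw the participant while the other lowers the dose and carries on, and both could claim to follow the text.

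What is at stake is the primary outcome of the participants affected. Conversion is read from retinal imaging at 12 months. Raised blood pressure or an arrhythmia may be a reason to change the bladder drug, but it does not prevent an eye examination. If the stop is taken to end participation, an outcome that could have been observed goes missing because of a rule. Since only mirabegron has a stated alternative to stopping, such losses could also differ between groups in a comparison that is not randomized.

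The sensitivity analysis is a separate and smaller matter. Removing early stoppers from the mirabegron group alone compares people who stayed on mirabegron with everyone on solifenacin. That selects on something that happens after baseline, in one group only, and so adds an imbalance to an analysis meant to test robustness.

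**Working it through.** **Stopping rule: the possible readings side by side.** No arithmetic applies here.

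1. *The whole study stops.* No dose would then be left to reduce, so the second half of the sentence has no meaning.
2. *The participant leaves the study.* This fits the section heading, and the triggers resemble participant-level exclusions in Table 1. It does not fit the dose-reduction clause. Nor does it fit section 2.3, where removing dose-adjusted participants from a sensitivity analysis implies that they are in the main data. It would also end follow-up before the 12-month timepoint, although section 2.2 plans visits for all patients.
3. *Only the drug stops, or its dose is lowered, and follow-up continues.* This agrees with sections 2.2 and 2.3, but the sentence does not say it.

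The third reading is the only one consistent with the rest of the article, and it is not the one written.

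**Planned losses.** The net sample size reproduces with the standard two-proportion formula (pooled variance under the null, two-sided 0.05, 80% power, 0.12 against 0.03, mean 0.075):

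n = [1.960 × √(2 × 0.075 × 0.925) + 0.842 × √(0.12 × 0.88 + 0.03 × 0.97)]² / 0.09² ≈ 133.3, so 134 per group, as stated.

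Enrolling 156 leaves 156 − 134 = 22 losses per group (22/156 = 14.1%). Rule-driven losses within that number cost no power beyond what is planned.

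**One-sided exclusion.** Inputs: the 12% conversion rate from section 2.3, set equal in both groups so that any difference is false; an excluded fraction f of mirabegron users (assumed 2%, 5%, 10%); and a ratio r of conversion risk in the excluded to that in the rest (assumed 0.5, 1, 2). The documents give neither f nor r.

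Group rate = (1 − f) × rest + f × r × rest, so rest = 0.12 / (1 − f + f × r).

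| r | f = 2% | f = 5% | f = 10% |
|---|---|---|---|
| 2 | 11.76% | 11.43% | 10.91% |
| 1 | 12.00% | 12.00% | 12.00% |
| 0.5 | 12.12% | 12.31% | 12.63% |

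Against 12% in the untouched solifenacin group, the false difference is 0.24, 0.57 or 1.09 points in favour of mirabegron at r = 2, zero at r = 1, and 0.12, 0.31 or 0.63 points against it at r = 0.5. The smaller fractions are more plausible, because entrants have already taken their drug for at least six months.

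**Does excluding from both groups cure this?** With the same f and r in both groups, both rates shift alike and the false difference is zero. With unequal fractions it is not. At r = 2, with 2% stopping mirabegron and 10% stopping solifenacin (assumed), excluding from both gives 0.12/1.02 − 0.12/1.10 = 11.76% − 10.91% ≈ 0.86 points against mirabegron. Excluding from mirabegron alone gives 0.24 points in its favour.

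**The case against.** The other side has several good arguments.

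- *The sentence is only loosely worded.* The heading, the resemblance to Table 1, the next sentence on an individual's right to withdraw, and the later mention of participants who stop or change dose all point to a participant-level rule. This stands. A reader might infer that a single event anywhere halts the whole trial; the context does not support that.
- *Dose reduction is permissive.* The text can be read as stop by default, or consider a lower dose. That softens the conflict, but whether the participant stays in follow-up is still unsettled. The article states this rule; it does not leave it to a fuller document.
- *The trigger may concern mirabegron only.* Only that drug is named, the surrounding text describes its cardiovascular profile, and section 2.2 ties cardiac monitoring to its safety. This is plausible, so the point does not rest on the rule covering both groups.
- *Outcome loss is conditional.* Sections 2.1 and 2.2 have all patients followed and evaluated to 12 months, and nothing says that eye visits end with the drug. This stands: outcomes are lost only if a centre takes the stop to mean withdrawal.
- *The sensitivity analysis matters little.* A protocol-adherent analysis not limited to one group is already planned, the clause on dose adjustment may cover both groups, and a mirabegron-only check could simply ask whether sustained exposure changes the result. These reduce the weight, but the stopping clause itself remains one-sided. The objection that excluding from both groups is no guaranteed cure is also right, as the last calculation shows.

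**Conclusion.** The point holds as a minor one. The stopping rule gives incompatible instructions, and one of its natural readings would discard primary outcomes that can still be observed and would contradict the analysis section. How many is unknown, since the documents give no event rate and the loss depends on how centres apply the rule.

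The one-sided exclusion is real but small: between 0.6 points against and 1.1 points for mirabegron under the assumed fractions and risk ratios, direction unknown, against a planned difference of 9 points. It touches one sensitivity analysis.

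Two stronger conclusions might be inferred and are not supported. One is a material loss of power: the attrition allowance comes first, and nothing shows that it would be exceeded. The other is bias in the primary comparison from the exclusion, which does not enter that analysis. No sample size, alpha or primary model changes.

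**What to change.** Replace the sentence in section 2.1 with, for example: *If severe hypertension, tachycardia or atrial fibrillation occurs, the treating clinician stops the participant's overactive-bladder drug or, for mirabegron, may lower the dose instead. The participant remains in the scheduled 6- and 12-month eye visits unless consent is withdrawn.* Dose reduction is limited to mirabegron because the article gives no solifenacin dose below 5 mg.

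In section 2.3, let the sensitivity analysis leave out participants of either group who discontinue their drug before month 6 or need its dose changed. Report the number left out per group, and note that the analysis still selects on a post-baseline event.

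The cost is wording. The visits are already planned for everyone. The one downside is a slightly smaller solifenacin group in that sensitivity analysis: 0.02, 0.05 or 0.10 × 134 = 2.7, 6.7 or 13.4, so about 3, 7 or 13 participants at assumed fractions of 2%, 5% or 10%.
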